**Usual maternity care**

(k=6)

**2YL Mentoring scheme** + usual maternity care

(k=6)

**Routine data collection after birth**

(data collector)

**Routine data collection after birth**

(data collector)

**Routine data collection 6 weeks**

(PHU routine visit)

Invitation to participate in future

interviews, focus groups, photovoice

**Routine data collection 6 weeks**

(PHU routine visit)

Invitation to participate in future

interviews, focus groups, photovoice

**Recruitment, consent, data collection** ≈**3-6 and** ≈**9-12 months**

Interviews, focus groups, photovoice

**(Routine data collection at 1year** (routine PHU visit)

**(Routine data collection at 1year** (routine PHU visit)

Figure 2. Two Young Lives pilot study flowchart

Randomisation

The unit of randomisation is the trial area (or cluster), rather than individual woman. The sixteen trial areas will be allocated cluster numbers. Randomisation will be managed via a secure web-based randomisation and data management system hosted by MedSciNet with telephone back-up available at all times. Randomisation to intervention sites (2YL) and control sites (usual care) will occur in a 1:1 ratio. A minimisation algorithm will be used to ensure balance between the groups with respect to PHU use and distance to referral hospital. MedSciNet will write the randomisation program and hold the allocation code.

Intervention: 2YL mentoring scheme + usual maternity care

Women in the intervention group will receive the 2YL mentoring scheme provided as an adjunct to usual maternity care. Using the TIDieR reporting guidance^11^, a description of the intervention is as follows:

*Brief name*. 2 Young Lives mentoring scheme for pregnant teenagers and young mothers in Sierra Leone.

*Why? Brief rationale*. A qualitative study in Eastern Freetown in 2017 examined the causes of the high incidence of maternal death in teenagers. Among the key findings was that pregnant girls are often abandoned or neglected by their families, particularly when being cared for by a non-parental adult. It is common for pregnant girls to then stay with a more distant relative or with her boyfriend’s family, sleeping on bare ground without a mosquito net, and being fed once a day in exchange for heavy domestic duties such as water collection and laundering. This lack of adult care or support often leads to delays in care seeking or complete lack of antenatal and delivery care, putting girls at high risk of death from untreated infections and anaemia, lack of birth preparation, and common obstetric risks. It was hypothesised that having a mentor could mitigate against the risks of maternal and infant mortality and morbidity in pregnant adolescents and their babies. A review of the determinants of delivery service use identified low maternal age as a determinant for not accessing skilled care for delivery ^12^, and evidence from other community projects in Freetown indicate that having an advocate when accessing health care helps to reduce some of the barriers such as disrespectful care and informal charges. There is strong evidence that connectedness with an adult, be it a parent or a non-parental adult, appears to be foundational for adolescent health and well-being more generally ^13-15^, including delaying rapid second pregnancies ^15^. Stakeholder engagement in October 2021 identified lack of awareness in schools of the government’s new policy on encouraging pregnant teenagers to stay in school or return to education after birth, and lack of confidence to be able to cater for pregnant girls and young mothers. This has prompted the inclusion of a teachers’ workshop in the pilot trial.

*What? (Materials).* 2 Young Lives training manual details the content and delivery activities for a 4-day training course for mentors. 2 Young Lives teacher training manual for a 2-day workshop for teachers. Welbodi health cards are a set of bespoke pictorial representations of common scenarios and maternal / newborn health issues, laminated and collated into sets.

*What? (Procedures) and How? (Modes of delivery)*. Weekly meetings between mentor and mentee; going to a local health facility with mentee to register for antenatal care, and reminding to attend or attending with mentee for usual antenatal care; accompanying mentee to health facility when in labour or needing emergency care (or ensuring other birth partner is available according to mentee’s wishes); flexible support postnatally dependent on mentee’s support network; discussion with mentee to consider small business options and accompanying mentee to purchase first supply of goods; monthly site meetings with all mentors and mentees for social interaction, cooking, eating and group discussion using Welbodi health cards; visits from mentor to mentee’s family to advocate for family support, if safe and appropriate; a face-to-face training for teachers in each of the 8 intervention sites. Graduation celebration at the end of the mentoring scheme.

*Who provided?* Mentors and teachers are trained by an experienced educationalist with experience of training both cadres. Mentors are women selected from communities where mentoring will take place, recruited based on having a reputation for kindness and being trustworthy, and an existing interest in young women’s issues. Visitors at monthly meetings are HCPs from local health facilities, or other or other community members who talk about educational or training opportunities.

*Where?* Mentoring takes place in agreed venues in the community where the mentee feels comfortable and where mentee and mentor can have a confidential conversation. Monthly meetings take place in a location in the community where there is shaded space for a group of 15-20 to cook (outdoors on a fire) and eat; many villages have these shared spaces, or mentors’ compounds where there is tree-shade.

*When and how much?* Girls are recruited at any stage of pregnancy, and have at least weekly mentoring as described, until baby is one year old.

*Tailoring?* If mentees are identified who have physical or intellectual disabilities, the programme is tailored to their needs where possible. For example, by providing communication cards for a deaf girl to use in labour, or by monitoring a girl with a learning disability taking pregnancy medication.

*Modifications? 10. How well planned? 11. How well actual?* These elements will be reported on at points in the research cycle when formative evaluation of implementation is undertaken.

Usual or routine maternity care is described below and will be the same in both intervention and control groups.

# Control: usual maternity care

Usual maternity care in Sierra Leone is comprised of the following components:

- 8 antenatal checks
- Screening for Hb, VDRL, Sickle cell status, malaria, urinalysis, HIV, Hep B
- Sulfadoxine-pyrimethamine (SP) as an intermittent preventive treatment (IPT) against malaria
- Free insecticide-treated bednet (ITN) at first antenatal visit
- Single dose Albendazole (worm medicine)
- Nevirapine for prevention of mother to child transmission of HIV (for all)
- Ferrous Sulphate
- Tetanus Toxoid immunisations x 2.
- Birth with a skilled birth attendant in a health facility with referral by ambulance for emergencies
- Post birth observation for 24 hours (or more if needed)
- BCG and Oral Polio Vaccine 0 for baby before leaving hospital
- 3-7 days postnatal check for mother and baby
- Baby immunisations starting at 6 weeks postnatal. Defaulters followed up in community by community health workers
- Free contraception

# Outcome measures

**Primary feasibility outcomes**:

Eligibility, recruitment, retention and attrition rates

Randomisation, data collection and data completeness

Selection of most appropriate primary outcome measure and sample size calculation

**Secondary maternal outcome**

Secondary maternal outcomes will include, for example, Intermitent Preventive Therapy (IPT) for malaria, anaemia, Number of Tetanus Toxoid immunisations, caesarean sections, blood transfurions, birth at facility, sepsis, postpartum haemorrage, place of birth and attendant, uptake of contraception.

**Secondary perinatal outcome**s

Secondary perinatal outcomes will include, for example, gestational age, birthweight, Apgar, newborn resusciatation, breastfeeding within 1 hour, Kanguroo mother care,

6 weeks postnatal immunisation updake, infant death at 1 year.

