# How the 2YL intervention may work

Overall, the aim of 2YL is that mentees and their babies survive birth and the postnatal period, and that these young women are empowered economically and socially to thrive. A theory of change diagram in Figure 1 in page 8 illustrates how and why the 2YL intervention may work in young women in Sierra Leone.

After community engagement with key community stakeholders, volunteer mentors are recruited and trained to support mentees across a number of domains. The 4-day manualised training programme uses discussion, role play and bespoke pictorial maternal health resources to learn and share important health messages. Key ingredients of the mentoring scheme include a weekly one to one meeting, promotion of health services uptake, monthly social gatherings for peer support and health discussions, advocacy and practical advice, support to start and run small businesses, and encouragement to return to education or start vocational training.

There are a number of mechanisms whereby being mentored could lead to improved health outcomes for mothers and their babies:

- Mentors ensure that girls access antenatal care, often paying for routine drugs when not available in the clinics, and directly observing the girls taking them. They ensure birth with a Skilled Birth Attendant, a proven life-saving intervention. In addition, the timeliness and quality of this care, and the quality of interaction with the girl in the health facility may be improved by the her being accompanied by a known and respected older woman in the community^9^; mentors are often allowed to be present for birth. Getting to know a health worker through monthly facilitated discussions and regular antenatal care could also increase girls’ confidence in the health service, increasing their likelihood of seeking care in labour or in an emergency. Similarly, having a trustworthy adult in their lives also allows mentees to ask advice of mentors and access care promptly.
- Girls are economically empowered through their small businesses, which could lead to a better diet in pregnancy, potentially addressing risk factors for maternal mortality such as malnutrition and anaemia. This economic empowerment could also allow girls to make independent decisions when to go to hospital as they could pay for their own transport^10^.

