Suboptimal maternal health care contributes to premature deaths, disability, and devastating spending in a country with an incipient financial crisis exacerbated by the 2014 Ebola epidemic (and further weakened during the ongoing COVID-19 epidemic). It has the highest maternal mortality rates in the world (1,360/100,000) with teens accounting for nearly 40% of all maternal deaths (more than two thirds caused by pre- eclampsia, haemorrhage and sepsis). Neonatal, infant and child mortality are also high (31.8, 83.5 and 11/1,000 respectively) and infants of mothers who die are up to 10 times more likely to die within their first 2 years. Antenatal attendance, access to skilled birth attendants and facility deliveries are low, and quality service delivery is often poor with disparities in access and availability to appropriate assessment and intervention, with delays in delivery, escalation of care and emergency maternity care.

Participants

Inclusion criteria

- Pregnant women aged under 18 at recruitment

Exclusion criteria

- There will be no exclusion criteria in terms of gestational age, as from an ethical and logistical standpoint, all young pregnant women should have access to the intervention, and pregnancy outcome data to be collected at an individual level.

Clusters and participant selection and enrolment

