# Data collection

Primary and secondary pregnancy outcome data collection

Outcome data will be recorded over the study period and will be collected at an individual level. Recent stakeholder engagement has identified the routine data collection tools used to collect routine data (ANC attendance register, birth register, referral register, 6-week postnatal check appointment book). At some PHUs, an additional ‘adolescent book’ is in use to record ANC registration of under-18-year-olds and associated birth outcomes). Regular visits to PHUs by data collectors will use these to identify under-18-year- presenting at the health facility (e.g. registering for ANC, delivering their babies in the PHU or in a referral hospital, or attending the PHU for the 6-week postnatal appointment) and will allocate each a unique study number which will be recorded in a book that is kept securely in the clinic in the same way as the clinic health registers. Routine practice is for women who do not return for infant immunisations at 6 weeks post-natal to be followed up in the community by a community health worker (CHW). This will allow for maternal deaths in the 42 days after birth, and for neonatal deaths up to 28 days to be included as part of the routine data collection. At the 6 weeks routine postnatal appointment, young mothers in both arms will also be given the option to individually enrol and participate in the sub-studies (e.g. qualitative interviews, photovoice), in order for qualitative data to be collected at around one year (e.g. experiences of care, acceptability, use of contraception, plans to return to education or training, business set up). As mentioned in the application, for those agreeing to participate in the sub-studies, explicit consent will be gained.). Adolescent girls identified by the research assistant who have a disability and/or recently completed the mentoring programme at pre-trial sites may also be invited to take part in the photovoice project. One year infant routine data will be collected from the infant immunisations registry.

The following table represents various scenarios and strategies for data collection in these scenarios:

| Scenario | Strategies to mitigate lost data |
| --- | --- |
| Girl attends ANC, gives birth at PHU and attends 6-week check at PHU | N/A |

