# Proposed analysis

We will undertake two statistical analyses: one pragmatic, intention to treat analysis (ITT) to compare intervention and control clusters that include all adolescent girls as originally allocated after randomization; and a complementary per protocol (PP) analysis to compare intervention and control clusters that includes only those girls who completed the intervention originally allocated. The CONSORT guidelines for reporting of parallel group RCTs recommend that both ITT and PP analyses should be reported for all planned outcomes to allow readers to interpret the effect of an intervention. It is not possible to blind clusters to interventions they receive, but outcome assessments will be blinded.

The main analysis will be pragmatic and by logistic regression adjusting the standard errors for clustering. This gives equal weight to each woman. A secondary analysis using random effects generalised least squares (GLS-RE) will also be attempted, although past experience is that the model might not converge to give any useable results. We will adjust for important baseline differences that might be related to outcomes (e.g. parity, gestation at first antenatal visits). As individual-specific data will be used there is a potential for missing data; but the main impact of missing data would be to invalidate the randomised comparison if there was unequal dropout between the two arms, leading to potential boas. Multiple regression, as described, would correct for any such bias.

Qualitative data from interviews with women and focus groups discussions with mentors, healthcare providers and stakeholders with be analysed using Braun and Clarke's six-phase approach to thematic analysis^18^. In brief, this includes familiarisation with the data, generation of initial codes, the searching for and review of themes, naming and offering explanations for each theme, and lastly producing a report. This practical analytic approach involves inductive coding practices which are both consultative and initially open^19^, and thus helpful to explore the perspectives of different research participants, highlighting similarities and differences, and generating unanticipated insights^18^.

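### Anaemia, sepsis, haemorrhage, birthweight and similar secondary outcomes are recorded through facility contact, which mentoring is meant to raise, and the planned regression cannot correct the resulting difference in recording between arms

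*Protocol*

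**What the plan says.** Protocol, Outcome measures, puts clinical events and use of services in one list of secondary maternal outcomes: "anaemia, Number of Tetanus Toxoid immunisations, caesarean sections, blood transfurions, birth at facility, sepsis, postpartum haemorrage, place of birth and attendant". The secondary perinatal outcomes include "gestational age, birthweight, Apgar, newborn resusciatation, breastfeeding within 1 hour".

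Data collection names the sources as the "routine data collection tools used to collect routine data (ANC attendance register, birth register, referral register, 6-week postnatal check appointment book". Data collectors use these to "identify under-18-year- presenting at the health facility", which is how a girl enters the data set. The scenario table in the same section adds cross-checks with the referral hospital, a visit to the registered address, contact with maternal-death investigators and community health worker follow-up at 6 weeks. Where it says what might be missed, it names only maternal death, stillbirth and neonatal death. Haemoglobin screening is listed as part of usual maternity care (Control: usual maternity care).

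On the intended effect of mentors, How the 2YL intervention may work says: "They ensure birth with a Skilled Birth Attendant, a proven life-saving intervention". The same section has them securing antenatal care, and the intervention description has them accompanying girls in labour and emergencies. On the setting, Study design, setting and population says: "Antenatal attendance, access to skilled birth attendants and facility deliveries are low".

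Proposed analysis plans an intention-to-treat comparison of all girls as allocated, plus a per-protocol one. It proposes adjustment for baseline differences, with parity and gestation at first antenatal visit as examples. It accepts that unequal dropout would undermine the randomised comparison, and then says the regression would put this right.

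**The concern.** The sources named for these outcomes work only when a girl has been seen. Anaemia needs a haemoglobin test. Sepsis, haemorrhage, birthweight, Apgar, resuscitation and breastfeeding in the first hour need someone at or soon after the birth to write them down. The intervention is designed to raise that contact. If it succeeds, the chance of being recorded differs by arm for a reason unrelated to the true frequency of the event.

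A working programme could then appear to go with more maternal morbidity, or a difference in either direction could come from who was assessed. The protocol treats this kind of problem as solved by regression, so nothing in it warns the analyst or reader.

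**Working it through.** The plan gives no facility-birth rate by arm and no rate for any of these outcomes, so there is no figure of its own to reproduce. Every rate below is an assumption.

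**1. Unrecorded counted as no event.** Let r be the true risk, equal in both arms, and f the share of recorded girls whose outcome is assessed. Recorded risk = r × f, so the recorded risk ratio = f(intervention) / f(control), whatever r is.

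- 60% v 75%: 75/60 = 1.25
- 60% v 90%: 90/60 = 1.50. With r = 8%, the recorded risks are 0.08 × 0.60 = 4.8% and 0.08 × 0.90 = 7.2%.
- 50% v 95%: 95/50 = 1.90

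**2. Some events captured outside a facility.** If a share s of events among unassessed girls is still found, recorded risk = r × (f + (1 − f) × s). With s = 0.3:

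- 60% v 75%: 0.825/0.72 = 1.15
- 60% v 90%: 0.93/0.72 = 1.29
- 50% v 95%: 0.965/0.65 = 1.48

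Partial capture shrinks the distortion but does not remove it.

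**3. Assessed girls only.** In the 8% example, dividing by assessed girls gives 4.8/60 = 8% and 7.2/90 = 8%, a ratio of 1.00, provided that assessed and unassessed girls have the same risk. If they do not, the bias is one of selection. Let a be the risk in girls who would reach a facility in either arm, and b the risk in those who reach one only because of mentoring. The control risk is a; the intervention risk is (f_C × a + (f_I − f_C) × b) / f_I.

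- a = 10%, b = 20%, 70% v 90%: (0.07 + 0.04)/0.90 = 12.2%, ratio 1.22
- a = 10%, b = 30%, 50% v 90%: (0.05 + 0.12)/0.90 = 18.9%, ratio 1.89
- a = 20%, b = 10%, 50% v 90%: (0.10 + 0.04)/0.90 = 15.6%, ratio 0.78

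The direction depends on b relative to a, which the protocol does not inform. Birthweight and Apgar belong here: without a measurement they are missing, not zero.

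**4. Whether regression corrects it.** Under step 1, take girls with the same parity and gestation. If f still differs by arm within that group, the recorded ratio there is again f_I/f_C, so adjustment returns the same false ratio. Under step 3, regression on assessed girls removes the bias only if the covariates account for the link between being assessed and the outcome. The protocol gives no reason to expect that of parity and gestation at first visit. The second is also observed after clusters are allocated, can be changed by a mentor who brings a girl in earlier, and does not exist for a girl without antenatal care.

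**5. Outcomes not affected in this way.** Caesarean section and transfusion take place in facilities, so their absence elsewhere is close to a true zero. With IPT, tetanus doses, antenatal checks, referral, facility birth and attendant, they measure uptake, and a rise may be a real effect.

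**The case against.** The strongest reply is that denominators and coding belong in a statistical analysis plan, which is not shown, and that nowhere does the protocol say unrecorded morbidity counts as no event. That is correct, and it means the 1.25 to 1.90 range is conditional on a coding rule the protocol neither adopts nor excludes. It does not dispose of the point. The data sources, the scope of tracing and the statement that regression corrects the bias are all fixed in the protocol, and a later plan does not make that statement right.

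Several limits stand:

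- Girls with no facility contact are not in the data set, so part of the distortion is selection into it, and the country's low facility use does not give f for the recorded girls.
- That no source outside facilities exists is a reading of the sources named. Home visits might yield some reports of sepsis or haemorrhage.
- Higher facility use is the intended effect, supported by an uncontrolled evaluation of 67 mentored women without a comparator rate for skilled attendance.
- Facility birth, attendant, antenatal checks and data completeness are already outcomes, and they supply much of what is needed to show the assessed proportion.

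A reader might also infer from "both ITT and PP analyses should be reported for all planned outcomes" that the trial commits itself to two between-arm comparisons of every secondary outcome. Those words report what the CONSORT guidelines recommend; the section plans both analyses but does not list the secondary outcomes they cover.

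**Conclusion.** The point holds as a risk of differential ascertainment that the protocol does not recognise for these outcomes and wrongly describes as correctable. With equal true risks, the false risk ratio is 1.25 to 1.90 on the assumed fractions if unrecorded means no event, and 1.15 to 1.48 if 30% of unassessed events are found. Among assessed girls the examples run from 0.78 to 1.89. The size in this trial is unknown until the assessed proportions by arm are known.

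Three stronger readings are tempting and are not supported. One is that the comparison will show harm, or that switching denominator reverses the sign: neither direction is established, and for birthweight and Apgar it can be either. Another is that the definitive trial's primary outcome will be chosen wrongly as a result. The pilot does aim to inform that choice, but it already names a mortality composite as its primary clinical outcome, directs its tracing at those events, and nowhere says that between-arm differences in morbidity will decide. The third is that between-arm estimates for these outcomes must be barred; a clear label is enough. This point does not challenge the primary composite.

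**What to change.** In Outcome measures and Proposed analysis, divide the secondary outcomes in two.

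- **Uptake outcomes**, compared between arms on all recorded girls: facility birth, attendant, antenatal checks, IPT, tetanus doses, caesarean section, transfusion and referral.
- **Outcomes seen only if assessed**: anaemia, sepsis, postpartum haemorrhage, birthweight, Apgar, resuscitation and breastfeeding within 1 hour. Code *not assessed* as its own category and never as no event. Report the assessed proportion by arm first, then the results among those assessed as descriptive. Label any between-arm estimate as subject to differential ascertainment, and do not read it as benefit or harm.

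Delete the statement in Proposed analysis that multiple regression would correct the bias from unequal missing data.

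The cost is protocol wording, one extra category on the electronic form and weaker statements on some secondary outcomes. Implementation was planned from May/June 2022 and this version is dated 21 July 2023, so records already entered may need recoding.
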